### Chronic Obstructive Pulmonary Disease

Patients will be identified through the use of GRASP COPD [13] and directed to the MISSION COPD clinics. At the clinics, patients will be reviewed according to the following the National Institute for Health and Care Excellence (NICE) quality framework standards [20]:

Diagnosis: Thorasys [21] and exhaled nitric oxide from Niox [22]Medicine optimization: Flo-Tone deviceSmoking cessationSelf-management: MISSION Self-Management Plans and myCOPD (similar to myAsthma but including online pulmonary rehabilitation program)

After the initial assessment, all patients will be encouraged and supported to keep themselves active while using myPR, the online pulmonary rehabilitation tool designed by my mHealth. Patients found to be at high risk of disease exacerbation (based on clinical characteristics or prior health care usage, decided by the senior clinician at the clinic) at the MISSION will be encouraged to report their symptoms via the Message Dynamics portal or Clinitouch system to allow early recognition and treatment of exacerbation.

### Breathlessness

#### Assessment

Patients with breathlessness who do not have an established diagnosis will be identified from the GP and practice records by using GRASP case-finding tools and will be offered the same high-quality diagnostic service as that offered to patients with asthma and COPD. In the MISSION clinic, these patients will be assessed using our novel diagnostic tools with additional availability of electrocardiogram recordings and a point-of-care test to identify any strain on the cardiac muscle by measuring the B-natriuretic peptide level. If asthma or COPD is identified, patients will join the respective care pathways. If a cardiac cause is identified, the patient will either be referred to the heart failure clinic or discharged to their GP. If the cause is a syndrome that leads to difficulty in breathing or deconditioning, patients will be offered an appointment with a MISSION ABC physiotherapist who will deliver targeted breathing retraining and discuss the benefits of maintaining exercise.

#### Innovations Embedded With New Models of Care

A brief outline of the innovations is provided below, followed by a description of how these innovations are incorporated into the new service model.

##### Digital Platforms to Identify and Monitor Patients

GRASP is a tool created by PRIMIS (Nottingham, United Kingdom) in conjunction with the University of Nottingham, United Kingdom. The tool examines GP records based on a chosen set of read codes and generates a search list tailored to the demands of the interrogator. This tool has been successfully used to generate patient lists for a variety of projects for the Wessex Academic Health Science Network (Southampton, United Kingdom).

##### Patient Self-Management and Monitoring

The following tools were used for patient self-management and monitoring:

###### MymHealth (myCOPD and myAsthma)

MymHealth [23] is a Web-based self-management system designed to support self-care in people with COPD and asthma. The system can be easily and securely accessed online by patients and HCPs. It facilitates the effective recognition of symptoms, inhaler technique, and management of medicines. It is an easy-to-use system that promotes patients to manage their COPD or asthma at home. Patients can also access an electronic platform containing a comprehensive, guided, 6-week pulmonary rehabilitation program to improve their health and quality of life.

###### Message Dynamics

Message dynamics [15] is a multiaward-winning provider of low-cost telehealth solutions through an app or a traditional telephone. Patients respond to a simple questionnaire that aims to detect symptoms of exacerbation.

###### Clinitouch

Clinitouch [16,17] is an app-based system that uses disease-control questionnaires and Bluetooth-enabled blood pressure and oxygen-saturation monitors that allow clinicians to remotely monitor their patient cohort. The patient is supported with an online self-management plan.

#### Technical Innovations

##### Diagnosis

The following tools were used for diagnosis:

###### Niox

This is a point-of-care testing device that measures exhaled nitric oxide [22]. It is a marker of eosinophilic corticosteroid-responsive inflammation that can predict loss of control in patients with asthma and supports phenotyping of patients with asthma and COPD. This tool was recently approved by NICE for the diagnosis of asthma [24].

###### Thorasys

This is a portable diagnostic tool that measures airways oscillometry, airway resistance, and obstruction independent of patient effort, thereby providing an accurate diagnosis with minimal effort [21,25]. Oscillometry offers an alternative method to traditional methods such as spirometry for assessing airway function. It has the potential to identify abnormal airway function that spirometry may be unable to detect, especially defects residing in the smaller airways. Oscillometry is particularly useful in patients who are unwilling or unable to adequately comply with the technical requirements of spirometry or when spirometry is considered inappropriate or contraindicated.

##### Treatment Improvement

For improving treatment, the following tools were used:

###### Clement-Clark Flo-Tone

This is a simple device that fits within the mouthpiece of any inhaler [26]. When the optimum inspiratory flow rate is achieved for that device, a musical note is heard. This immediately provides feedback to the patient but can also be recorded via a mobile phone app to inform the HCP.

###### Airsonett

The Airsonett device [19] can improve care of patients with severe allergic asthma and poorly controlled symptoms. The laminar airflow system, placed above the patient during sleep, vastly reduces aeroallergen exposure, resulting in fewer symptoms and improves disease control.

##### Service Model Innovations - MISSION COPD and MISSION Asthma

This is an award-winning, novel way of delivering highly specialized multidisciplinary asthma and COPD care in the community, providing specialist clinics to rapidly identify patients with asthma and COPD and then to assess and adjust management plans and empower patients through education [27]. A pathway has been designed to improve patient care and safety and prevent hospital admissions and nonelective visits in primary care.

### Aims and Objectives

This study aimed to examine (1) the implementation of a novel integrated care model for patients with airways disease and undifferentiated breathlessness using both quantitative and qualitative evaluation of processes and patient and HCP experiences and (2) clinical outcomes throughout the clinic cycles driving a continuous improvement process, evaluated through participatory action research. We also aimed to establish whether MISSION ABC, including innovative diagnostic and self-management tools, can deliver improvements in health service use and clinical outcomes for different patient groups (asthma, breathlessness, and COPD) by comparing the 12-month period prior to the first patient attendance and the 6-month period following attendance, by using regressional analyses to control for seasonal variation bias.

## Methods

### Study Design

#### Summary

The main focus of this project is to deliver a quality-improvement project—MISSION ABC—that has been informed by three prior projects. This protocol of predominantly Participatory Action Research [28] accompanies the project to record the delivery, iterative changes to the project, and outcomes and ensure rigor in the reporting of these parameters.

Accompanying innovations are embedded in the project to encourage a culture of growth amongst small- and medium-sized enterprises within the health care system. Outcomes related to these innovations are exploratory, not designed to be powered, and will not be presented with a control group.

A combination of study designs are required to evaluate all aspects of the service:

Participatory Action Research approach involving real-time evaluation at each clinic to inform subsequent clinicsCohort (longitudinal) data approach for clinic- and patient-level service use and outcome indicatorsBefore-and-after study of patient outcomes before and after the clinic visitQualitative methods (interviews and focus groups)

#### Participatory Action Research Approach

##### Data Evaluation

A list of all the data that will be evaluated on a cyclical basis is provided below. These include quantitative data and themes that will be explored qualitatively with HCPs, patients, and carers to inform the next clinic. Issues for improvement, changes to the clinic process, and the rationale for changes will be recorded in a learning log. The impact of changes will be reviewed following the subsequent clinic visit and from any further feedback from qualitative interviews and focus groups. Fidelity to the original project plans and reasons for the changes made will be reported as part of the project analysis.

This list of outcomes is not exhaustive, as the cyclical approach may identify other key areas that are important to monitor. If additional questionnaires or methods of data collection from patients are required, they will be submitted to the ethics committee as an amendment.

##### Clinic Process

Acceptability of clinic delivery model by patients, carers, and HCPs including host GP surgeriesPerceived appropriateness of the clinic by the patient group, judged by HCPs delivering the clinic services and the host surgeriesPrimary care staff attendance at the clinic (number and position)Number of patients identified as appropriate for the clinicAttendance rates at each offered session

##### Diagnostics

Number of new or modified diagnoses made at the clinicNumber of patients where the British Thoracic Society Asthma stage or Global Obstructive Lung Disease (GOLD) COPD classification [5] is changed following discussion by the multidisciplinary teamNumber of new comorbidities newly identified

##### Education and Supported Self-Management

Uptake of the education sessions when offered and reasons for decline, when givenAcceptability of education sessions by participants and carersConfidence in self-management measured before and after the clinic visit and after subsequent education sessionsChanges in treatment adherence before and after the intervention, measured using the Adherence Starts with Knowledge questionnaire-12 (ASK-12) [29,30] and a prescription reconciliationUptake of the HCP education programAcceptability of the HCP education program by participants

##### Use of Treatment Tools

Number of patients who showed improved inhaler technique, as judged after the first clinical encounterNumber of patients with improved technique who sustained the improvement at subsequent review when prompted by clinical needNumber of quit-for-life reviews that resulted in a quit attempt, and if these quit attempts resulted in sustained cessation at 6 monthsNumber and type of inhalers prescribed before and after the intervention

##### Remote Monitoring

Number of patients identified for remote monitoringNumber of triggers on remote monitoring that progress to a clinically significant exacerbationNumber of reported delays in reporting exacerbation due to the presence of remote monitoringIncidences where the carer of a family member is required to facilitate use of remote monitoring

##### Additional Balancing Measures

Number of GP or practice nurse sessions changed or cancelled to host the clinicAdditional costs such as childcare or extra travel incurred by the delivery team when care is delivered remote to their usual place of work or outside the usual working weekNumber of GP, community nurse, or emergency department episodes resulting from remote monitoringNumber of secondary care referrals resulting from the program

#### Patient and Health Service Use Outcomes (Longitudinal Follow-Up)

Changes in quality-of-life measures prior to the clinic visits and at 3 and 6 months were measured with generic or disease-specific quality-of-life questionnaires. These questionnaires evaluated the following:

Changes in productivity and activation measures prior to the clinic visit and at 6 monthsChanges in disease control, quality of life, and comorbidity measured by disease-specific questionnaires and unscheduled health care utilization (eg, emergency GP visits, out-of-hours/111 calls, hospital admissions, and emergency department attendances).Exacerbations in the 6 months before and after MISSION attendanceCost of delivery of the clinic model

#### Innovations

##### Thorasys

Number of new diagnoses of airways disease made after use of the Thorasys deviceNumber of patients who are unable to complete reproducible spirometry who have reproducible results with ThorasysNumber of unusable resultsPerceived ease of use by health care professionals

##### Flo-Tone

Number of patients given the Flo-Tone deviceNumber of patients using the Flo-Tone device following reviews, when prompted by clinical needNumber of patients deemed to have improved the pressurized metered dose inhaler technique through use of Flo-Tone

##### Airsonett

Number of patients suitable for use of the Airsonett temperature-controlled laminar airflow device

Number of patients offered the device who accepted its useChange in exacerbation frequency in the 6 months before and after the use of the Airsonett deviceNumber of patients who elect for ongoing use of the device after 6 months

##### MyCOPD and MyAsthma

Uptake of online, supported self-management provided by my mHealthAcceptability of online-supported self-management by the patient and family or carerNumber of patients using online pulmonary rehabilitationNumber of patients who access the online self-management plan

##### Message Dynamics

Acceptability of the treatment by patientAcceptability of the treatment by HCPsNumber of positive triggers that can be managed by advice onlyNumber of positive triggers that require clinical review, and type of review chosenNumber of triggers that result in a clinically significant exacerbationDuration of monitoring required by the patient, as judged by the clinical team

##### Clinitouch

Acceptability of the treatment by patient

Acceptability of the treatment by HCPsNumber of positive triggers generated by Bluetooth device readingsNumber of positive triggers generated by symptom scoresNumber of positive triggers that can be managed by advice onlyNumber of positive triggers that require clinical review, and type of review chosenNumber of triggers that result in a clinically significant exacerbationDuration of monitoring required by the patient, as judged by the clinical team

### Study Participants

#### Study Setting

MISSION Clinics will be held in at least 10 surgeries within the Wessex region. The clinic services will be delivered by an integrated team of primary (primary care nurses and GPs), secondary (respiratory nurses, physiotherapists, physiologists, and registrars), and tertiary (regional specialist asthma service) care providers with delivery of care across all three sectors.

#### Overall Description of Study Participants

Adult patients (aged ≥ 16 years) with poorly controlled asthma or COPD as well as those with undifferentiated breathlessness will be identified using GRASP tools; referred from a community pharmacist or by their primary care team; and invited to a local MISSION clinic with a relative, friend, or carer in attendance, if they wish. All eligible attendees will be invited to participate in the study. The sample size will be determined by the uptake of appointments and clinic capacity but is projected to be 500 patients and 15 HCPs.

#### Eligibility Criteria

All patients who have attended the MISSION ABC clinic will be considered eligible to partake in the study if they are able to provide informed consent. Family or carers will be asked to participate in the qualitative research if they have accompanied the patient to an educational event. Health care participants from host surgeries or visiting from outside organizations will also be eligible for participation in the participatory action research and qualitative aspects of the study. An individual’s participation in any applicable aspect of the MISSION will be unaffected by their decision to consent.

### Study Procedures

#### Screening and Enrollment

All potential participants will be sent a Participant Information Sheet by post or email after initial contact. If they are suitable for the clinic, they will be screened for their ability to give informed consent. If they are able to consent and wish to do so, they will be enrolled at a clinic. It will be made clear to each participant that their care is unaffected by their decision to enroll in the study.

#### Randomization

There will be no randomization.

#### Study Assessments

The study assessments are summarized in Figures 1, 2, and 3 (COPD, asthma, and breathlessness, respectively).

#### Patient Assessments

##### Patient Characteristics

Age, height, weight, and body mass index recorded at the first clinic visitNew or changed diagnoses recorded for each patient seenAny change in British Thoracic Society Asthma Stage or GOLD COPD classification, as judged by the multidisciplinary team for those with newly diagnosed or established asthma or COPDNumber and type of comorbidities pre-existing and identified through the MISSION processOccupation, employment status, and postal codeSmoking status

##### Disease Control, Disease-Related Quality of Life, and Activation Measures

All baseline questionnaires will be sent to patients before the first clinical encounter. If they choose not to participate in the research study, these questionnaires will still aid in clinical decision-making and will be retained in the clinical record. If patients need assistance in completing these questionnaires, it will be offered at the first clinic visit. The questionnaires used are listed below:

A baseline exploratory semistructured questionnaire designed by the team to explore disease impact and behaviorsDisease-specific control questionnaires (Asthma Control Questionnaire [31] and COPD Assessment Test [32]): Baseline measure and then repeated at 3 and 6 months after the first clinical encounterExercise tolerance and symptom measures: Veterans Specific Activity Questionnaire [33], Nijmegen questionnaire [34], and Self Evaluation of Breathing Questionnaire [35] at baseline and repeated at 3 and 6 monthsUse of unscheduled care (including GP visits), steroids or antibiotics for exacerbations, and hospital admissions recorded for each patient at 3 and 6 months compared to their 6 and 12 months visits prior to the MISSION processMeasures of activation and medicine compliance (ASK-12 and Patient Activation Measure [36]) at baseline and 3 and 6 monthsProductivity measures (EuroQoL-5D [37] and Work Productivity and Activity Impairment [38]) at baseline and 6 monthsQuality of life scores: Short Form Health Survey-36 (generic) [39], Asthma Quality of Life Questionnaire (AQLQ) for asthma [40], and St George’s Respiratory Questionnaire for COPD [41]Number of quit-for-life reviews that have resulted in a quit attempt at 3 and 6 monthsPrescription reconciliation at 6 months before and after the clinic visit to assess medication usage

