**Objective:**

This mixed-methods protocol examines the implementation of a novel integrated care model for patients with airways disease and undifferentiated breathlessness by using both quantitative and qualitative evaluation of processes, patient and health care professional experiences, and clinical outcomes throughout the clinic cycles. It aims to establish whether Modern Innovative Solutions to Improve Outcomes in Asthma, Breathlessness, and Chronic Obstructive Pulmonary Disease (MISSION ABC), including innovative diagnostic and self-management tools, can deliver improvements in health service use and clinical outcomes for the different patient groups (asthma, breathlessness, and COPD) and compares the 12-month period prior to the first patient visit and the 6-month period following the last visit.

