#### Analysis of Quantitative Outcome Data

The objective of all analyses is to examine differences in measured variables between time points.

The following comparisons will be made:

Asthma Control Questionnaire, CAT, and AQLQ: baseline as compared to 3 and 6 monthsEmergency care outcomes: 3 and 6 months prior to study as compared to the 3- and 6-month study periodActivation or medicine compliance (ASK-12 and Patient Activation Measure): baseline as compared to 3 and 6 monthsEuroQoL-5D and weight-bearing physical activity: baseline as compared to 3 and 6 months

All the abovementioned variables are continuous measures. Comparisons between time points will be made using the paired *t* test or the Wilcoxon matched-pairs test, depending on the distribution of the changes in outcome between time points.

Summaries of the measures of monitoring and supported follow-up will be prepared (measures outlined above). Patient satisfaction measures will be summarized descriptively. Numbers and percentages will be used for categorical variables, whereas mean and SD or median and interquartile range will be used for continuous variables. Uncertainty in percentages, means, and medians will be quantified by calculating the appropriate 95% CIs.

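### The before-and-after windows for health-service use contradict each other in length and starting point, and the window in the objective is not the one in the analysis section

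*Protocol article*

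**What the plan says.** Five places in the protocol article set a window for health-service use or exacerbations.

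- **Abstract, Objective:** the study "compares the 12-month period prior to the first patient visit and the 6-month period following the last visit".
- **Introduction, Aims and Objectives:** improvement is to be established by "comparing the 12-month period prior to the first patient attendance and the 6-month period following attendance", and this is to be done "by using regressional analyses to control for seasonal variation bias".
- **Methods, Patient and Health Service Use Outcomes (Longitudinal Follow-Up):** exacerbations are compared over the 6 months before and the 6 months after MISSION attendance.
- **Methods, Disease Control, Disease-Related Quality of Life, and Activation Measures:** unscheduled care, steroids or antibiotics for exacerbations, and admissions are "recorded for each patient at 3 and 6 months compared to their 6 and 12 months visits prior to the MISSION" process.
- **Data Analysis, Analysis of Quantitative Outcome Data:** emergency care outcomes are compared over "3 and 6 months prior to study as compared to the 3- and 6-month study" period. The test is the paired t test or "the Wilcoxon matched-pairs test, depending on the distribution of the changes in outcome between time points". The regression for season does not appear here.

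The section A New Model of Care describes a one-stop or a two-stop clinic journey, so first and last visit need not be the same day.

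**The concern.** Improvement in health-service use is a stated aim, and the Discussion says the outcomes will inform decisions on future service implementation. The study has no randomisation, and this aim is answered by comparing patients with their own earlier experience. The windows therefore define the effect being estimated. With several definitions in print and none said to govern, the same data can give different answers, and the choice could be made after the results are known.

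Three things are at stake.

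- **Length.** Some of the stated pairs are 2:1. Counts over a window half as long are lower whether or not the service works.
- **Starting point.** Beginning the post-period at the last visit leaves out events that occur while a two-stop patient is already in the service.
- **Baseline.** Asthma patients are selected for features such as frequent exacerbations, emergency department visits and admissions. Look-backs of 3, 6 and 12 months may then give different baseline rates, even after scaling to a common unit of time.

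**Working it through.** The article gives no event rate, power calculation or expected effect, so there is no stated figure to reproduce.

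**1. The definitions side by side (months)**

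| Place | Before | After | After/before | Post-period starts |
|---|---|---|---|---|
| Abstract, Objective | 12 | 6 | 6/12 = 0.50 | last visit |
| Aims and Objectives | 12 | 6 | 6/12 = 0.50 | attendance |
| Longitudinal Follow-Up (exacerbations) | 6 | 6 | 6/6 = 1.00 | attendance |
| Assessment list, read in order | 6 and 12 | 3 and 6 | 3/6 = 6/12 = 0.50 | not stated for this item |
| Data Analysis | 3 and 6 | 3 and 6 | 3/3 = 6/6 = 1.00 | study period, start not defined |

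No single pair satisfies all five rows.

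**2. What unequal length does to raw counts.** Let a patient have a constant rate λ per month and no effect of the service. Over b months before and a months after, the expected counts are λb and λa. Their ratio is λa/λb = a/b, whatever λ is.

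- 12 before, 6 after: 6/12 = 0.50, an apparent fall of 50%.
- 6 before, 3 after: 3/6 = 0.50, the same.
- 6 and 6, or 3 and 3: 1.00, no artefact.

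At an assumed 2 events per year, the expected counts are 2.0 over 12 months and 1.0 over 6. Simulated means were 1.99 and 1.00.

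**3. What the named tests would do with such counts.** The simulation used 400 runs per setting, gamma-Poisson counts with shape 1, and no effect. The event rates (0.5, 1, 2 and 4 per year) and the two-sided 0.05 level are assumptions, because the article gives neither. Enrolment "is projected to be 500 patients and 15 HCPs"; 150 and 50 stand for possible cohort sizes. The table gives the rejection rate across the assumed rates, for the paired t and Wilcoxon tests together.

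| Windows | N = 500 | N = 150 | N = 50 |
|---|---|---|---|
| 12 vs 6 | 100% | 93 to 100% | 47 to 100% |
| 6 vs 3 | at least 99% | 73 to 100% | 27 to 97% |

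With equal windows (6 vs 6 or 3 vs 3), rejection was about 3 to 7% over all sizes and rates. With 400 runs, the simulation error around 5% is √(0.05 × 0.95/400) = 1.1 percentage points, so this is close to nominal.

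**4. The starting point.** For a one-stop patient, first and last visit coincide and nothing is lost. For a two-stop patient with g months between visits, the Objective ends the pre-period at the first visit and starts the post-period at the last. Expected events left out of both periods are λg. The article does not state g, so the size cannot be given.

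**5. The regression in the Aims.** Its stated purpose is season. It would remove a difference in window length only if it modelled a rate or carried an offset, which is not stated.

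**The case against.** The strongest reply is that the halving does not arise in the analysis that the article specifies. Data Analysis is the only section that attaches a named test to these outcomes, and its windows are equal. The exacerbation outcome, and the same outcome for the Airsonett device, also use equal 6-month windows. In the body text, the 12-against-6 comparison comes with regression, not with a simple difference in counts. Offsets and scaling to rates are details that an article may leave to the full protocol or SAP. The assessment list is loosely worded and may only describe which look-back data are collected; a 6-against-6 comparison could also be drawn from it. The five places do not name exactly one endpoint either: they range from health service use in general to exacerbations and emergency care.

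Most of this stands, and it rules out two stronger readings. A reader might infer that the trial will report a spurious 50% fall. The documents do not support that: it needs raw counts over unequal windows, and no section prescribes that combination. A reader might also infer that the assessment list times health-service use from the first clinical encounter. That phrase belongs to the asthma and COPD control questionnaires; the unscheduled-care item names no starting point.

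The contradiction itself remains. The windows are not omitted for an SAP to supply: they are stated, incompatibly, in the objective, aims, assessments and analysis. An SAP could choose one but could not agree with all of them. The outcomes overlap enough to collide, since the assessment list includes steroids or antibiotics for exacerbations as well as admissions.

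**Conclusion.** The point holds as an unresolved contradiction over which window and which starting point govern, and not as a demonstrated bias in the final analysis. Followed literally, Data Analysis is free of length bias but does not answer the objective's 12-against-6 question. The objective's windows, put through the paired tests on raw counts, would give an expected ratio of 0.50 under no effect. That ratio assumes only a constant event rate. The rejection rates also depend on the assumed event rates, the gamma-Poisson shape and the 0.05 level. The assessment list counts as a 2:1 definition only on the in-order reading. The conflict between last visit and attendance stands on the Objective and the Aims alone, although the Aims may simply be less specific; its effect is confined to two-stop patients and cannot be sized. Separately, the seasonal adjustment promised in the Aims has no counterpart in Data Analysis.

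**What to change.** State one window pair and one anchor, in the same words, in all five places: the Objective, the Aims, Longitudinal Follow-Up, the assessment list and Data Analysis.

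- **Anchor.** End the pre-period the day before the first MISSION visit and start the post-period at the first visit, so that events between visits count as post.
- **Window, option A.** Use the equal 6-against-6 windows already in Data Analysis, with 3 against 3 as secondary.
- **Window, option B.** If the 12-month look-back is kept, compare events per patient-month in a count model with a log person-time offset, and never compare raw counts.
- **Season, under either option.** Carry the adjustment promised in the Aims into Data Analysis. Neither option deals with season by itself: two adjacent 6-month windows cover different halves of the year, and an offset on 12 against 6 corrects length only. A paired test cannot hold a season term, so the adjusted comparison needs the regression to be written down.

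The cost is wording in five places and one model specification. No new data should be needed, provided that events were extracted with dates, which the article does not say. The Results section reports enrolment complete and analysis under way, so the choice should be fixed and dated before results are reported.
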